## Abstract

**Introduction:**

Health problems in sport cause a major burden on several pillars: sport clubs, health and insurance system and mostly the individual athlete. There is limited knowledge in supporting dual-career athletes firmed on evidence-based research in injury/illness prevention, load and stress management. The main goal of this research approach is to determine how specific physical, psychosocial and dual-career loads affect the occurrence of injuries and illnesses in elite handball players and how much of a variation in the athlete’s load leads to an occurrence of an injury/illness. A secondary aim is to determine the association between objective and subjective measures of stress as well as examine the benefits of certain biomarkers to monitor stress, load and injury/illness occurrence in athletes.

**Methods and analysis:**

This prospective cohort study, as part of a PhD project, will be carried out on 200 elite handball players of first men's handball league in Slovenia during an entire handball season, lasting from July 2022 to June 2023. Primary outcomes, including health problems, loads and stress, will be assessed weekly on a player level. Other player-related outcomes will include anthropometry, life event survey and blood biomarkers (cortisol, free testosterone and Ig-A), which will be taken three to five times across the observation period according to the players’ training cycle.

**Ethics and dissemination:**

The project was approved by the National Medical Ethics Committee of Slovenia (number: 0120-109/2022/3) and will be conducted in compliance with the most recent version of Helsinki Declaration. The study results will be published as peer-reviewed articles, congress presentations and as a Doctoral thesis. The results will not only be of importance for the medical and sports community for development of new injury prevention and rehabilitation strategies but also for structuring the correct policy recommendations for athletes’ general health.

**Trial registration number:**

NCT0547129.

STRENGTHS AND LIMITATIONS OF THIS STUDYThis longitudinal study will investigate the associations between different types of load and injury/illness occurrence in elite handball players.The study will implement holistic monitoring of athlete’s health with objective and subjective measures.The association between objective and subjective measures of stress in athletes will be investigated.The study focuses exclusively on elite male handball players, which can be seen both as a strength and also as a limitation when it comes to generalisability.The work has direct implications for sports/clinical practice; periodical athlete monitoring could be beneficial in terms of preventing health issues, lowering health system costs, supporting dual career of athletes, structuring sound policies and enhancing both sports and academic performance.

## Introduction

Regular moderate exercise is known to have positive health benefits^1^; from preventing a number of non-communicable diseases to improving cardiorespiratory fitness and consequently decreasing cardiovascular morbidity and mortality.^1–3^ Top-level sports, on the other hand, are associated with an increased risk of illness and injury.^4 5^ There has been a number of studies^6–12^ showing a high prevalence of health issues that include injuries and illnesses among elite athletes, ranging from 20% in athletes of all ages^4^ to 45% in youth athletes.^5^ The injuries and illnesses are not only limiting athletes for the time being^13^ but also represent a major burden for sport clubs, health and insurance system and can as well be the reason for sports’ career termination.^14–18^

### Athlete’s stressors

Sports and non-sports loads pose stress on athletes, leading their physical and psychological well-being from homeostasis to acute fatigue, over-reaching, overtraining, subclinical immune changes, clinical symptoms, illness/injury and possibly death.^19^ Research points out that inadequate load management is an important independent risk factor for the development of acute illness and overtraining syndrome.^9 19 20^ However, it is not yet possible to quantify how much an increase in training load leads to an increased risk for a given illness^19^ or injury.^21^ Furthermore, the literature states that there is a risk of illness when an athlete is exposed to other lifestyle stressors that affect the immune system, including sleep deprivation or severe psychosocial stress,^22^ such as major life events.^23^ A special group of athletes, that might be at higher risk for health problems, are dual-career (DC) athletes. They are posed to the challenge of combining their education/work with elite sport, suggesting their overall weekly load is higher compared to non-athlete students and athletes who are not in the education process. It was found that the highest levels of stress and illness incidence in student-athletes arise during the academically stressful periods.^24 25^ Thus, the relationship between stress and physical health is especially relevant for DC athletes, who often face multiple physical and psychosocial stressors (such as transitioning between schools/campuses and home life, frequent travel, academic load and sports load).^26–28^

### Health monitoring and load management

One potential strategy for injury and illness prevention in elite sports is monitoring of external and internal loads. Monitoring an athlete’s workload has a number of potential benefits, including interpreting performance changes, increasing understanding of exercise responses, detecting fatigue and monitoring recovery needs, optimisation of the training programme and competition calendar. It also serves for providing adequate workload levels to reduce the risk of injury and illness^29 30^ and guide rehabilitation programmes. External and internal loads can be assessed with subjective and objective measures. External load measurement typically involves quantifying an athlete’s training or competition loads by reporting training hours, running length, amount of weight lifted, number of games played and other external factors such as life events, everyday problems and/or travel. On the other hand, internal load is measured by assessing the internal biological, physiological and psychological response to an external load^31^ such as heart rate or ratings of perceived exertion. A recent systematic review of internal stress monitoring has identified subjective reporting to be more sensitive and consistent than objective measurements in determining acute and chronic changes in an athlete’s well-being.^32^

### Biomarkers

Biomarker discovery and validation is a critical aim of the medical and scientific community.^33^ Biomarkers can be used as an objective assessment tool for health, performance, recovery and talent identification in elite sport. Among the most critical hormones for athletes seem to be cortisol, testosterone, dehydroepiandrosterone and immunoglobulin-A (Ig-A). However, testosterone to cortisol (T:C) ratio is considered to be more sensitive to training stress than either measure alone,^33^ as several studies report poor performance outcomes and suboptimal training adaptations in athletes with a low T:C ratio.^34 35^ However, to the best of the authors’ knowledge, no previous work has examined the use of biomarkers for injury prevention, recovery after an injury or identification of individuals at increased risk.

Given all of the above, there is a need for better health surveillance, load monitoring and support services with an emphasis on injury/illness prevention and rehabilitation.^36^ As DC athletes have a wider variety of loads that pose greater psychophysiological strain to them, they could also be at an increased risk for injury/illness. Therefore, more comprehensive monitoring of potential risk factors in this specific population is warranted. It is not yet known, but important to determine how much of overall load can an athlete withstand before injury/illness occurs. Thus, the primary aim of this study is to determine how specific physical, psychosocial and DC loads affect the occurrence of injuries and illnesses in elite handball players and how much of a variation in the athlete’s load leads to an occurrence of an injury/illness. A secondary aim is to determine the association between objective and subjective measures of stress as well as examine the benefits of certain biomarkers to monitor stress, load and injury/illness occurrence in athletes.

## Methods and analysis

### Study design

The study is designed as a prospective cohort study. All measurements will be conducted over a single handball season, lasting from July 2022 to June 2023 (a total of 46 weeks), with weekly reporting (table 1) and three to five biomarker sampling timepoints (figure 1). We used the Standard Protocol Items: Recommendations for Interventional Trials (SPIRIT) checklist when writing our report.^37^

**Figure 1 F1:**
[figure not shown]
Assessment plan. LESCA, Life Events Survey for Collegiate Athletes.

**Table 1 T1:** Questionnaires and tests

Test/questionnaire	Outcome	Purpose
**SDSCQ**	Age, sex, level of education, sport, years of training, player position, previous injuries	General information about the athlete
**Anthropometry**	Body height (cm), body weight (kg)	Measure of basic anthropometric characteristics of an athlete
**LESCA**	Major life events score	Measure of life stress
**OSTRC**	Weekly health problems (acute and overuse injuries, illnesses), measured as prevalence and incidence and severity as OSTRC-severity score and time-loss days	Identifying health problems
**Weekly load and stress**		Monitoring of athlete’s load
	Training load in hours	
	Competition load in minutes	
	Academic load in hours	
	Work load in hours	
	Average daily sleeping hours	
	Perceived stress on scale 1–10	
**Blood biomarkers**		Monitoring of stress/insufficient recovery and/or health problem risk
Cortisol	Cortisol values in nmol/L	
Free testosterone	Free testosterone values in pmol/L	
Ig-A	Ig-A values in g/L	
	Free testosterone: cortisol ratio	

LESCA, Life Events Survey for Collegiate Athletes; OSTRC, Oslo Sports Trauma Research Center Questionnaire on Health Problems; SDSCQ, Sociodemographic and Sports-Career Related Questionnaire.

### Participants and sample size

A power analysis was a priory determined using the G*Power software.^38^ Based on previous studies with similar design, we expected to find nearly two times as high odds of injury occurrence in athletes during a period of high academic stress compared with low academic stress (OR=1.78; effect size (ES)=0.14)^25^ with power of 0.90 and α=0.05, two-tailed, which calculated an initial sample size of 134 participants. As in sports practice, the athlete drop-out is to be expected (due to travelling, international transfer to another club/state, etc); we adjusted the originally calculated sample size by following formula: N1=n/(1−d),^39^ where N1 is adjusted sample size, n is the sample size required as per the proposed formula (N=134) and d is the drop-out rate (d=0.10). This resulted in total sample size of 149 athletes. Inclusion criteria will be as follows: DC and non-DC registered male handball players who are competing in the first Slovenian handball league and are above 18 years of age.

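### The 134 in the sample size section matches a sign-test count of informative units, not of participants, so 90% power is not established for 134, 149 or 200 athletes

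*Protocol article*

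**What the plan says.** The Participants and sample size section of the protocol article bases the study size on one contrast, the "odds of injury occurrence in athletes during a period of high academic stress compared with low academic stress". The inputs are "OR=1.78; effect size (ES)=0.14", taken from a cited earlier study. The software is named ("A power analysis was a priory determined using the G*Power software") but the test is not. The result is given as follows: "with power of 0.90 and α=0.05, two-tailed, which calculated an initial sample size of 134 participants". Dividing by 1 − 0.10 for drop-out leads to the final statement: "This resulted in total sample size of 149 athletes".

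Three other places bear on this.
- The abstract plans a larger cohort: the study "will be carried out on 200 elite handball players".
- Study design sets 46 weeks of weekly reporting.
- Statistical analysis plans a logistic regression that accounts for repeated observations within each athlete.

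The sample size section gives no injury risk, no share of athletes whose status differs between the two periods, no share of high-stress weeks and no split between dual-career and other players.

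**The concern.** An odds ratio of 1.78 for a binary outcome is a modest effect, and 134 participants is few for 90% power unless every participant is informative. In a within-athlete comparison of two periods, an athlete injured in both or in neither contributes nothing to a sign or McNemar test. A required number of informative units must therefore be divided by the share of athletes expected to be informative before it becomes a number to recruit. The article adjusts only for drop-out.

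This is the only power statement in the article. If its unit is wrong, readers have no sound basis for judging what a non-significant association between academic load and injury would mean, and such a result could be taken as stronger evidence of no association than it is.

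**Working it through.** **Inputs from the article.** OR 1.78; ES 0.14; power 0.90; two-tailed α 0.05; N = 134; drop-out 0.10; planned cohort 200; 46 weekly reports.

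**Step 1: reproduce 134.** Under a sign test, the chance that an informative unit falls on the high-stress side is p = OR/(1 + OR) = 1.78/2.78 = 0.640. The effect size is g = p − 0.5 = 0.140, which is the stated ES. Exact binomial test of p = 0.5 with at most 2.5% per tail, power at p = 0.64:

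| n | Power |
|---|---|
| 132 | 0.896 |
| 133 | 0.884 |
| 134 | 0.9035 |

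The smallest n with power of at least 0.90 is 134 (actual α 0.0465).

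Other calculations do not link the three figures:
- chi-square with w = 0.14: 537
- paired t-test with dz = 0.14: 539
- two independent proportions at OR 1.78: 512 to 1,136 in total, for base risks between 10% and 50%
- repeated-measures ANOVA with f = 0.14 and two times: 136
- multiple regression with f² = 0.14 and six predictors: 131

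The last two come close to 134, but neither effect size follows from OR 1.78, which converts to d = 0.318 and f = 0.159.

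**Step 2: drop-out.** 134/(1 − 0.10) = 148.9, rounded up to 149. This step is correct.

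**Step 3: from informative units to athletes, one high/low pair per athlete.** Let ψ be the share of discordant athletes. Their number among N athletes is Binomial(N, ψ), and power is the sign-test power averaged over that distribution. The article does not give ψ. If the periods are independent, with risk p0 in the low-stress period and p1 = 1.78·p0/(1 − p0 + 1.78·p0) in the high-stress period, then ψ = p0(1 − p1) + p1(1 − p0). The values of p0 below are assumptions. The 20% and 45% are the Introduction's figures ("high prevalence of health issues that include injuries and illnesses among elite athletes, ranging from 20% in athletes of all ages", up to 45% in youth), which are prevalences of any health issue and not injury risks in a low-stress period.

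| p0 | p1 | ψ | N = 134 | N = 149 | N = 200 |
|---|---|---|---|---|---|
| 10% | 0.165 | 0.232 | 28% | 31% | 43% |
| 20% | 0.308 | 0.385 | 48% | 52% | 66% |
| 45% | 0.593 | 0.509 | 60% | 65% | 79% |

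Under independence the largest possible ψ is 1/(1 + 2√(p(1 − p))) = 1/(1 + 2√(0.640 × 0.360)) = 0.51, so the last row is practically the ceiling. Positive within-athlete association lowers ψ further. Without the independence assumption, 90% power needs ψ of essentially 1 at N = 134, 0.92 at 149 and 0.69 at 200.

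**Step 4: the planned weekly model, roughly.** Power ≈ Φ(ln(1.78)·√I − 1.96), with I = N·s·46·q(1 − q)·r(1 − r)/D. Here s is the share of athletes with academic load, q the share of high-stress weeks, r the weekly risk and D a design effect for clustering. All four are assumptions. For N = 200:

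| s | q = r | D | I | Power |
|---|---|---|---|---|
| 1.0 | 0.2 | 3 | 200·1·46·0.16·0.16/3 = 78.5 | above 99% |
| 0.5 | 0.2 | 3 | 39.3 | 95% |
| 1.0 | 0.1 | 3 | 200·1·46·0.09·0.09/3 = 24.8 | 82% |
| 0.3 | 0.1 | 6 | 3.73 | 20% |

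Over s from 0.3 to 1, q = r of 0.1 or 0.2, and D from 1 to 6, power at N = 134 to 200 runs from about 15% to above 99%.

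**The case against.** The strongest reply is that the shortfall in step 3 belongs to an analysis that the article does not plan. Reducing each athlete to one yes/no per period discards most of 46 weekly reports. With the weekly data, 134, 149 or 200 athletes may well reach 90%. This stands. A reader might infer from the 28% to 79% figures that the study is underpowered at all three sizes. The documents do not support that: step 4 shows power on either side of 90%, and the deciding inputs are not stated. Even for one pair per athlete, the ceiling of 0.51 rests on independence or positive association, which is plausible but assumed.

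A second reply is that the test is inferred, and its unit even more so. This also stands in part. The match of OR, ES and N to a sign test is hard to explain otherwise, but it does not show what was counted. If high- and low-stress exposure are equal and 1.78 is read as a rate ratio, injury events split 0.64 to 0.36 in the same way, so 134 could be events rather than discordant athletes. Under neither reading is 134 a number of participants.

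Third, the planned 200 exceeds 149. That gives some margin but does not repair a calculation made in the wrong unit.

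**Conclusion.** The concern holds in a limited form. The figure of 134 is, by strong inference, the n of an exact two-sided sign test. It counts informative units, has been read as participants, and has been enlarged only for drop-out. It also does not address the repeated-observations logistic model. The 90% power is therefore not established for 134, 149 or 200 athletes.

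On the calculation's own terms (one binary pair per athlete, independent periods), power is at most about 60%, 65% and 79% respectively. For the analysis actually planned, the article does not allow power to be stated, and it may be above or below 90%. The finding is that the power claim is unsupported, not that the cohort is shown to be too small.

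**What to change.** In Participants and sample size:

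1. Withdraw the statement that 134 participants give 90% power.
2. Name the G*Power test that was used and say what its n counts. The authors should confirm this from their own records and not adopt the reconstruction given here.
3. Restate power at the planned cohort of 200 less 10% drop-out (200 × 0.90 = 180) for the weekly repeated-observations logistic model at OR 1.78. Tabulate it over assumed values of weekly injury risk, share of high-academic-stress weeks, share of athletes with academic load, and within-athlete correlation. The share with academic load matters because players without a dual career are eligible and may contribute little or no contrast.

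The cost is one rewritten paragraph, a short table and a modest simulation or approximation. The stated power may become less favourable. No change in recruitment is proposed.

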### Statistical analysis

Statistical analysis will be performed using standard statistical software (SPSS V.27.0, IBM, Armonk, New York). Descriptive statistics will be used for all variables. Normality of data distribution will be assessed using the Shapiro-Wilk test. In case of non-normally distributed data, non-parametric statistics will be used, otherwise, the statistics for normally distributed data will be used. The data will be analysed using a logistic regression model to properly account for the dependency induced by the repeated observations over time within each subject. Main effect of all dependent variables on injury/illness occurrence will be studied using repeated measures analysis of variance (ANOVA) with time (preparation period vs competition period vs off-season period) as within factor, while group (injured/ill vs healthy) as between factor. Where significant effects will be found for group, time effects or two-way interactions, pairwise comparisons will be used to address the significant differences for each variable independently. For comparison of the groups, we will use independent t-test. The magnitude of effect for all dependent variables will be reported as partial eta squared (η^2^). In addition, *Cohens’ d* (ES) will be used to assess magnitude of difference between groups. Furthermore, regression analysis will be used to assess predictive power of individual parameters to identify injury/illness occurrence. For the correlation of subjective measures of stress with the objective measures, bivariate correlation will be used. Additionally, Bland-Altmann analysis will be used (low/high stress normative values) as previously recommended.^42^ Furthermore, receiver operating characteristic (ROC) curve analysis will be used for defining the cut-off values. Hypotheses will be accepted or rejected at p≤0.05.

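### The 0.90 power is for high versus low academic stress but counts players who may not study, and no planned analysis names that contrast

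*Protocol article*

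**What the plan says.** **Sample size.** The Participants and sample size section expects "nearly two times as high odds of injury occurrence in athletes during a period of high academic stress compared with low academic stress". It gives this effect as an odds ratio of 1.78 and an effect size of 0.14. For 0.90 power at a two-sided α of 0.05 it arrives at 134 players. It then divides by one minus the drop-out rate, where "d is the drop-out rate (d=0.10"), and reaches 149. This is the only power statement in the article. The Abstract gives the planned cohort as 200 players.

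**Population.** The same section admits "DC and non-DC registered male handball players who are competing in the first Slovenian handball league". It gives no minimum number and no expected share of dual-career players or of players in education. The Introduction (Athlete's stressors) describes dual-career athletes as "combining their education/work with elite sport", so a dual-career player may study, work, or do both.

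**Exposure.** The Weekly load and stress questionnaire records academic hours and work hours separately each week. Its 1–10 rating is of overall stress, not academic stress. No section defines a period of high or low academic stress.

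**Analysis.** The Statistical analysis section plans a logistic regression for repeated observations within subject, without naming an exposure. It continues: "Main effect of all dependent variables on injury/illness occurrence will be studied using repeated measures analysis of variance (ANOVA"). The ANOVA factors are season period (preparation, competition, off-season) and group (injured/ill, healthy). A further regression on individual parameters also names no exposure. The low/high stress wording there belongs to the Bland-Altman comparison of stress measures.

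**The concern.** The powered contrast needs players who pass through both high and low academic stress. A player who does not study has no academic hours in any week, and so has no high period to set against a low one. The 134 nevertheless counts every enrolled player. If a sizeable part of the league is not in education, the power for the one hypothesis that was sized is well below the 0.90 stated.

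The analysis section then leaves that hypothesis without a named test. The only contrasts it spells out follow the training calendar and the injury status. A reader could not tell from the article which estimate the 0.90 refers to, in which players it will be made, or what counts as high academic stress.

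**Working it through.** **Step 1. Reproduce the plan's figure.** Inputs from Participants and sample size: OR 1.78, ES 0.14, power 0.90, two-sided α 0.05, drop-out 0.10. The article does not name the test. An exact two-sided binomial test of p = 0.5 (sign or McNemar type) ties these figures together:

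- p = OR/(1 + OR) = 1.78/2.78 = 0.640
- g = p − 0.5 = 0.140, which is the stated ES
- At N = 132 the power is 0.898. At N = 134 it is 0.905, with actual α 0.0465. The smallest N reaching 0.90 is 134.
- 134/(1 − 0.10) = 148.9, rounded up to 149

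The arithmetic is therefore sound. It fits a within-athlete comparison, in which each counted athlete has both a high- and a low-stress period. Other calculations that were tried do not give 134. Two independent groups need about 510 to 1,140 in total, for assumed baseline risks of 10% to 50%. A two-measure repeated-measures ANOVA with f = 0.14 and correlation 0.5 needs 136.

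**Step 2. Count who can contribute.** Let s be the share of players in education. The documents do not give s. The main range below, 30% to 50%, is an assumption, and 75% and 100% are added for comparison. Usable n = enrolled × 0.90 × s, rounded, and power comes from the same exact test.

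| Share s | 149 enrolled: n | Power | 200 enrolled: n | Power |
|---|---|---|---|---|
| 100% | 134 | 0.905 | 180 | 0.965 |
| 75% | 101 | 0.81 | 135 | 0.89 |
| 50% | 67 | 0.64 | 90 | 0.76 |
| 30% | 40 | 0.39 | 54 | 0.51 |

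Exact power moves in small steps, so 135 gives 0.893 although 134 gives 0.905.

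**Step 3. Share or enrolment needed.** To retain 134 students:

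- With 149 enrolled, essentially every player must study (134/134).
- With 200 enrolled, 180 are retained, and 134/180 = 74% must study.
- At s = 50%, enrolment must be 134/(0.50 × 0.90) = 298. At s = 30% it must be 134/(0.30 × 0.90) = 497.

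**Step 4. Why these powers are optimistic.** In a sign or McNemar-type test, N counts athletes whose injury status differs between the two periods. Athletes injured in both periods or in neither add nothing. With s = 50% and an assumed 50% discordant, enrolment would be 134/(0.50 × 0.50 × 0.90) = 596. The powers in Step 2 treat every student as informative.

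**Step 5. Look for the contrast in the analyses.** The ANOVA contrasts are season period and injured/ill versus healthy. The t-test compares groups. The logistic and regression models name no exposure. High versus low academic stress appears in none of them by name, and no section says how weekly hours become high or low.

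**The case against.** **The hypothesis may well be tested.** A reader might infer that the powered hypothesis is not analysed at all. The article does not support that. The primary aim covers dual-career loads, academic hours are collected weekly, and both the repeated-observation logistic model and the regression on individual parameters could include them. An odds ratio for academic load is a natural product of either. A condensed article also commonly leaves covariate lists to the full plan. This stands, and it limits the point to a contrast that is neither named nor defined. It does not repair the power statement, which the article itself makes for one contrast while counting a wider population.

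**Non-students may contribute something.** A reader might also take it as fact that non-students have zero academic load and add nothing. Zero load is inferred from the description of dual-career athletes and from the separate recording of academic and work hours; no section says it outright. That such players add nothing holds for a purely within-player analysis. A population-averaged or random-intercept logistic model would also fit the article's wording, and there non-students supply low-exposure weeks. They also help to estimate the effects of training, match load and season. The gain for the academic contrast is modest. Under an illustrative person-week formula (8 high-stress weeks of 46, weekly injury risk 2% to 3%, none of it from the article except the 46 weeks), 67 students alone give power 0.56 to 0.72. Adding 67 non-students raises this to 0.62 to 0.79. That gain assumes the same baseline risk in both groups.

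**The planned cohort is larger than 149.** The Abstract's 200 players soften the shortfall, as Step 2 shows, but remove it only at a share of about 74% or more.

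**Season as a proxy.** Season period standing in for academic stress would confound it with training and match load. The article does not propose this, so it is no part of the point.

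**Conclusion.** The point holds in this limited form. The article claims 0.90 power at 134 players for high versus low academic stress, and counts all dual-career and non-dual-career players without an expected share in education. Players not in education contribute little or nothing to that contrast, so the stated power is not what the design delivers unless most of the cohort studies. If 30% to 50% study, power is about 0.39 to 0.64 with 149 enrolled and about 0.51 to 0.76 with 200.

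These figures rest on three assumptions: the student share, the exact sign-type test as the calculation behind 134 (it reproduces the OR, ES and N, but the article does not name it), and every student being informative. The third makes the figures optimistic.

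The analyses of the other loads in the whole cohort are not affected. This should be corrected, but it does not undermine the study as a whole.

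**What to change.** 1. In Participants and sample size, name the test behind 134 and say that the 0.90 power applies to players in education. Give their expected number at the planned enrolment, and restate the power at that number.
2. In Statistical analysis, define high- and low-academic-load weeks from the weekly academic hours. Name as the test of the powered hypothesis the within-player odds ratio of a new injury for high- against low-load weeks, in players in education, adjusted for season period and for training and match load.
3. Keep the whole-cohort models for the other loads in the primary aim.

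The cost is a change of wording and a lower stated power for this contrast. No new data and no extra recruitment are needed. If the academic contrast is not meant to carry the sample size, the alternative is to base the sample size on the load–injury model that will be fitted in all players.
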